**Trial registration number:**

ClinicalTrials.gov ID number NCT04708171 (PROGRAM-study), NCT03861299 (SAFE-trial)

Strengths and limitations of this studyFirst multicentre prospective study directly comparing awake mapping, asleep mapping and no mapping for glioblastoma resections in or near eloquent areas.International, multicenter design on a large scale, which will be of substantial benefit with regard to subgroup analyses and external generalisability of the results.Observational design will not exclude all possible, inherent forms of bias.

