## Methods and analysis

### Study design

This is a international, multicenter, prospective, three-arm cohort study. Eligible patients are operated using awake mapping, asleep mapping or no mapping with a 1:1:1 ratio with a sequential computer-generated random number as subject ID. Patients with motor-eloquent tumours will be treated in all study arms, while speech-eloquent tumours will only be treated in either the awake mapping or no mapping arm. The PROGRAM study (prospective cohort study of high-grade glioma resections using awake craniotomy and intraoperative stimulation mapping) is similar to the SAFE-trial (SAFE surgery for glioblastoma patients: awake craniotomy versus craniotomy under general anesthesia: a multicenter randomized controlled trial) and is initiated by the same center, however, the presented study will be different in various ways: the PROGRAM study (1) will be an observational, prospective cohort study, (2) will include asleep mapping as an additional treatment arm, (3) will evaluate the extent of resection of the non-contrast-enhancing part of the tumour as well, (4) will include both WHO grade III and grade IV gliomas, (5) will include an oncofunctional score as one of the outcomes and (6) will include neurosurgical centers in the USA and is part of the ENCRAM Research Consortium.^18^

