### Study objectives

The primary study objective is to evaluate the safety and efficacy of resections with or without mapping techniques (neurological morbidity and extent of resection) in HGG patients as expressed by National Institute of Health Stroke Scale (NIHSS) scores and volumetric data. Secondary study objectives are to study the overall survival (OS), progression-free survival (PFS) and oncofunctional outcome after resections with or without mapping techniques as expressed by survival data, progression on MRI scans and combining postoperative volumetric/functional outcomes, respectively.

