### Study procedures: clinical evaluations and follow-up

Preoperative (baseline) CRF (Case Report Form).Unique subject ID, demographics (centre, year, gender, age), tumour-specific factors (tumour volume preoperative, tumour hemisphere and lobe; eloquent areas), patient specific factors: preoperative KPS, ASA score, neurological status (NIHSS), MRC grade arm/leg (for motor-eloquent tumors), neurolinguistic testing, MOCA, QoL questionnaires (QLQ-C30, QLQ-BN20, EQ-5D).Surgery CRFType of ISM, surgeon’s rationale for modality, surgeon’s goal, use of preoperative steroids (if yes: clinical improvement, conversion to mapping possible); use of surgical adjuncts (if DTI: integrity of tracts), use of additional imaging, radiological factors: resection percentage (both the contrast-enhancing and non-contrast-enhancing part), residual volume and postoperative ischaemia.Follow-up CRFsSix weeks postoperatively: histology and molecular markers (WHO grade, MGMT status, IDH-1 status), neurological status (NIHSS), MRC grade arm/leg, status MRC arm/MRC leg/facialis/speech/visual (new, worsened, improved, stable), KPS, QoL questionnaires (QLQ-C30, QLQ-BN20, EQ-5D).Three months postoperatively: neurological status (NIHSS), MRC grade arm/leg, status MRC arm/MRC leg/facialis/speech/visual (new, worsened, improved, stable), KPS, neurolinguistic testing, MOCA, QoL questionnaires (QLQ-C30, QLQ-BN20, EQ-5D).Six months postoperatively: neurological status (NIHSS), adjuvant treatment, MRC grade arm/leg, status MRC arm/MRC leg/facialis/speech/visual (new, worsened, improved, stable), KPS, MOCA, QoL questionnaires (QLQ-C30, QLQ-BN20, EQ-5D).Twelve months postoperatively: PFS, OS (end of study).

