### Secondary study parameters

The Kaplan-Meier method will be used to estimate PFS and OS proportions per treatment group at appropriate time points, while the Greenwood estimate of the SE (standard error) will be used to construct the corresponding 95% CI. Multivariate cox proportional hazards models will be built for PFS and OS where treatment group effect will be corrected for minimisation factors age group (≤55 years vs >55 years), KPS (80–90 vs >90) and left or right hemisphere. Additionally, competing risk analysis will be used to calculate cumulative incidence of PFS (with competing risks progression/relapse and death without progression/relapse which add up to 100% at every time point). Oncofunctional outcome will be evaluated using a scatter or bubble plot with volumetric data on the x-axis and neurological status (NIHSS) or patient performance (KPS) on the y-axis. SAEs in both groups will be described.

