### Study monitoring

No scheduled on-site monitoring visits will be performed. Local investigators will remain responsible for the fact that the rights and well-being of patients are protected, the reported trial data are accurate, complete and verifiable from source documents and the conduct of the trial is in compliance with the currently approved protocol/amendment(s), with GCP (Good Clinical Practice) and with the applicable regulatory requirement(s). Direct access to source documentation (medical records) must be allowed for the purpose of verifying that the data recorded in the CRF are consistent with the original source data. No data safety monitoring board will be installed: all interventions are care-as-usual and patients are allocated without randomisation.

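### The oncofunctional outcome, a stated secondary objective of a non-randomised study, is evaluated only by a plot, so it yields no arm estimate, interval or case-mix adjustment

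*Protocol article*

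**What the plan says.** Study objectives in the protocol article makes this outcome an aim of the study: "Secondary study objectives are to study the overall survival (OS), progression-free survival (PFS) and oncofunctional outcome after resections". Secondary outcome measures defines it as one coordinate per patient, with extent of resection or residual volume on the x-axis and the postoperative change in NIHSS on the y-axis.

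Secondary study parameters gives its analysis: "Oncofunctional outcome will be evaluated using a scatter or bubble plot with volumetric data on the x-axis". There the y-axis is neurological status (NIHSS) or performance (KPS). No estimate, interval, test or covariate is named.

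For survival, the same section says: "The Kaplan-Meier method will be used to estimate PFS and OS proportions per treatment group at appropriate time points". Greenwood 95% CIs accompany these. Cox models for PFS and OS are corrected for age group, KPS and hemisphere. Cumulative incidences are added, with no adjustment stated.

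On allocation, Study monitoring says: "all interventions are care-as-usual and patients are allocated without randomisation". The surgery CRF records the surgeon's "rationale for modality", and Study design says: "speech-eloquent tumours will only be treated in either the awake mapping or no mapping arm".

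**The concern.** The Discussion frames the study as a balance between maximal resection and preserved function. The oncofunctional outcome is the only outcome that joins the two in the same patient, and Study design lists it among the features that set this study apart from its sister randomised trial. A plot cannot say by how much the arms differ on that balance, or how certain the difference is. Because the surgeon chooses the modality, points from different arms may also sit apart merely because different tumours went to different arms. If a numerical summary is chosen only after the plot has been seen, the choice is data-driven.

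**Working it through.** **1. How each outcome is analysed (Primary and Secondary study parameters).**

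| Outcome | Stated analysis | Estimate with interval or test | Adjusted |
|---|---|---|---|
| NIHSS deterioration | logistic regression, 4% level | yes | yes, one factor per 10 events if fewer than 40 events |
| No residual tumour | logistic regression, 1% level | yes | yes |
| OS, PFS (hazard) | Cox model | yes | age group, KPS, hemisphere |
| OS, PFS (proportion) | Kaplan-Meier, Greenwood CI | yes | no |
| Progression; death without progression | cumulative incidence | estimate | none stated |
| Oncofunctional outcome | scatter or bubble plot | **no** | **no** |

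Both components are modelled with adjustment as primary endpoints. Their combination is not modelled at all.

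**2. Axes.** The definition puts change in NIHSS on the y-axis. The analysis puts NIHSS status or KPS there. A status score carries the patient's baseline deficit, which a change score removes, so the plotted quantity is not the defined outcome.

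**3. Can case mix differ?** Yes. Allocation is not randomised and the modality follows a recorded rationale. For eloquence, the arms differ by rule, since the asleep arm has no speech-eloquent tumours. The size of the resulting bias cannot be derived from the document.

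**4. Would a yes/no composite do?** Take success as no residual contrast-enhancing tumour and no NIHSS deterioration at 6 weeks. The inputs from Sample size are: clearance 25% (no mapping) and 50% (mapping); deterioration 10% and 3%; 137 per arm. Assume resection and deficit are independent.

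- No mapping: 0.25 × 0.90 = 22.5%. Mapping: 0.50 × 0.97 = 48.5%.
- Power at two-sided 5%, unadjusted, n = 137 per arm: Φ{[|p₁−p₂| − 1.96√(2p̄(1−p̄)/n)] / √([p₁(1−p₁)+p₂(1−p₂)]/n)}.
- 22.5% v 48.5%: (0.260 − 1.96 × 0.0578)/0.0556 = 2.64, power 99.6%.
- Clearance alone, 25% v 50%: power 99.2%.
- No neurological benefit (10% in both arms): 0.50 × 0.90 = 45%; 22.5% v 45% gives 98%.
- Mapping doubles deterioration to 20%: 0.50 × 0.80 = 40%; 22.5% v 40% gives 88%, still in favour of mapping.

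The composite is nearly the resection endpoint again. The two dimensions have to be reported jointly and kept visible.

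**5. The four-way table.** Under the same assumptions, the expected shares are:

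| | Clear, no deterioration | Clear, deteriorated | Residual, no deterioration | Residual, deteriorated |
|---|---|---|---|---|
| No mapping | 22.5% | 2.5% | 67.5% | 7.5% |
| Each mapping arm | 48.5% | 1.5% | 48.5% | 1.5% |

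Deteriorations in total: 137 × 0.10 + 274 × 0.03 = 21.9. By the plan's own rule (10 events for arm, then one factor per 10), a yes/no function component supports about one covariate. Change in NIHSS kept as a score would bear fuller adjustment.

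**6. Survival illustration (assumed figures, not in the document).** There is no treatment effect, and 12-month OS is 60% in the reference arm.

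- Case mix worth a hazard ratio of 0.90 gives 0.60^0.90 = 63.1%; 0.80 gives 0.60^0.80 = 66.5%. The spurious gain is 3 to 6.5 points.
- A second assumption: OS 70–90% in good-prognosis and 50% in poor-prognosis patients. Good-prognosis shares of 60% v 50% give a raw difference of 2 to 4 points. Shares of 70% v 40% give 6 to 12 points.
- The 95% half-width for a difference with 137 per arm is about 10 to 12 points.

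**The case against.** Secondary outcomes may be descriptive, both components already have adjusted primary analyses, and the authors concede that "Observational design will not exclude all possible, inherent forms of bias". Modelling detail is also often left to an analysis plan that is not shown. This stands in part: the gap is a joint summary, not a total neglect of resection and function. But the article does not leave the method open. It names the plot as the evaluation, and followed exactly it leaves a stated objective without an estimate.

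A reader might infer that all the secondary outcomes apart from the hazard ratios are raw displays, so that the survival comparison is unadjusted. The document does not support that. Kaplan-Meier proportions with Greenwood CIs are estimates with intervals, no test between them is stated, and the between-arm comparison is the adjusted Cox model. Crude curves beside an adjusted hazard ratio are ordinary reporting.

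A reader might also infer that arm differences simply show case mix. The document supports only that treatment effect and case mix are mixed, in unknown proportion.

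The objection to standardising survival from the Cox model also has force. With only age group, KPS and hemisphere, the model omits grade, tumour volume and eloquence, so it removes only part of any confounding.

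**Conclusion.** The point holds for the oncofunctional outcome: as planned, it has no arm estimate, interval or adjustment, and the plotted y-axis departs from the definition. This follows from the text and needs no assumption. The amount of confounding is not computable from the document. The composite calculations rest on the planning rates, independence of resection and deficit, and an unadjusted test. They show why one yes/no composite would not answer the objective, however high its power. For survival there is a smaller point only: the 12-month proportions per arm are legitimate to show but are not comparable between arms without adjustment. The 2 to 12 points are an illustration under assumed prognosis.

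**What to change.** 1. Reconcile the axes: keep the plot, drawn as in Secondary outcome measures, with change in NIHSS at a fixed visit such as 6 weeks. Any KPS version should be labelled as additional.
2. Pre-specify covariate-adjusted arm differences with 95% CI for both coordinates together (residual volume or extent of resection, and change in NIHSS). Alternatively, use the four-way classification of residual tumour by NIHSS deterioration. In either case, show the function component separately so that resection does not dominate.
3. Adjust for the baseline factors in Primary study parameters (grade, preoperative neurological morbidity, preoperative volume, age, location/eloquence), as far as the number of events allows. Restrict contrasts with the asleep arm to motor-eloquent tumours.
4. Beside the Kaplan-Meier figures, give 12-month OS and PFS per arm standardised from the Cox model, with CI. Add grade, volume and location/eloquence to that model as event numbers allow, and note that residual confounding remains.

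The cost is analysis wording and some programming. The CRFs already collect NIHSS, volumes, OS and PFS. The downside is reliance on model assumptions. This is a cheap improvement.

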### Outcomes

#### Primary outcome measures

The primary outcomes are (1) proportion of patients with NIHSS deterioration at 6 weeks, 3 months and 6 months postoperatively; deterioration is defined as an increase of at least one point on the total NIHSS score compared with this score at baseline and (2) residual tumour volume of the contrast-enhancing and non-contrast enhancing part, as assessed by a neuroradiologist on postoperative T1 with contrast and T2/FLAIR MRI scan sequences using manual or semiautomatic volumetric analyses (Brainlab Elements iPlan CMF Segmentation, Brainlab AG, Munich, Germany or similar software).

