#### Secondary outcome measures

The secondary outcomes are (1) PFS at 12 months defined as time from diagnosis to disease progression (occurrence of a new tumour lesions with a volume greater than 0.175 cm^3^, or an increase in residual tumour volume of more than 25%) or death, whichever comes first; (2) OS at 12 months defined as time from diagnosis to death from any cause; (3) oncofunctional outcome defined as the calculated coordinate of the extent of resection (or residual volume) on the x-axis and the postoperative NIHSS deterioration (delta NIHSS) on the y-axis and (4) frequency and severity of serious adverse events (SAEs) in each arm.

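### The oncofunctional outcome is defined with change in NIHSS, but its analysis plots neurological status or KPS, so definition and analysis disagree

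*Protocol article*

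**What the plan says.** Under Secondary outcome measures, the Protocol article defines the oncofunctional outcome as a point in two dimensions. The horizontal position is "the calculated coordinate of the extent of resection (or residual volume) on the x-axis" and the vertical position is "the postoperative NIHSS deterioration (delta NIHSS) on the y-axis".

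Under Secondary study parameters, the analysis reads "Oncofunctional outcome will be evaluated using a scatter or bubble plot with volumetric data on the x-axis". For the vertical position, that section names "neurological status (NIHSS) or patient performance (KPS) on the y-axis". No model, adjustment or reference to baseline is stated for this outcome. For PFS and OS, the same section does state covariate correction.

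Three other places bear on how to read this:

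- **Study procedures: clinical evaluations and follow-up.** The baseline form lists "preoperative KPS, ASA score, neurological status (NIHSS" among its items, and the term neurological status is used again for the 6-week, 3-month and 6-month forms.
- **Primary outcome measures.** When the article means a change, it says so: "deterioration is defined as an increase of at least one point on the total NIHSS score compared with this score at baseline".
- **Study monitoring and Study design.** The article states that "patients are allocated without randomisation" and that "speech-eloquent tumours will only be treated in either the awake mapping or no mapping arm".

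**The concern.** An outcome and its analysis should refer to the same variable. Here they differ in two ways: a change score in the definition becomes a status in the analysis, and a second scale, KPS, appears as an alternative without having been part of the definition.

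The difference matters more in a cohort than in a randomised trial. A score taken after surgery contains whatever deficit the patient had before surgery. Without randomisation, nothing in the design makes preoperative deficit similar across arms. Case mix also differs by design, because speech-eloquent tumours are not treated with asleep mapping. The article itself lists preoperative neurological morbidity among the factors for its primary model (Primary study parameters). A plot of postoperative status by arm could therefore mix where patients started with what surgery did.

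At stake is the interpretation of a named secondary endpoint, which Study design lists as one of six features that set this study apart from the related randomised trial.

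**Working it through.** The article gives no sample size, power or significance level for this outcome, so there is no stated figure to reproduce. The check compares the two texts and then uses a short identity.

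**Step 1. The two descriptions side by side.**

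| Element | Secondary outcome measures | Secondary study parameters | Compatible? |
|---|---|---|---|
| x-axis | extent of resection or residual volume | volumetric data | Yes; the second is a looser term that covers the first |
| y-axis, NIHSS | delta NIHSS | neurological status (NIHSS) | No, if status means the score at a visit |
| y-axis, KPS | absent | offered as an alternative | No |

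**Step 2. What status means here.** The article uses neurological status for an item on the preoperative form. At that visit there is no earlier score to subtract, so the term cannot mean a change there. It recurs on the three follow-up forms. The natural reading is the score recorded at the visit. KPS is a different scale and cannot be shorthand for delta NIHSS, so the second mismatch stands however status is read.

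**Step 3. Consequence of a literal reading.** For patients with both values,

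mean postoperative NIHSS = mean baseline NIHSS + mean delta NIHSS.

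Taking the difference between two arms,

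gap in postoperative NIHSS = gap in baseline NIHSS + gap in delta NIHSS.

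Write d for the baseline gap. If surgery has the same effect in both arms, the gap in delta is 0 and the gap in postoperative NIHSS is d. The same identity holds for KPS.

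**Step 4. Illustration on assumed inputs.** The article gives no baseline NIHSS, so d was varied from 0 to 2 points. The assumptions were 137 patients per arm (the per-arm number under Sample size), Poisson baseline scores with mean 1 in one arm and 1 + d in the other, and the same 10% chance of a one-point rise in both. For d = 1 the expected means are 1 + 0.1 = 1.1 and 2 + 0.1 = 2.1, so the postoperative gap is 2.1 − 1.1 = 1.0 and the delta gap is 0.1 − 0.1 = 0. Simulation gave:

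| Assumed d | Gap in postoperative NIHSS | Gap in delta NIHSS |
|---|---|---|
| 0 | 0.00 | 0.00 |
| 0.5 | 0.50 | 0.00 |
| 1 | 1.00 | 0.00 |
| 2 | 2.00 | 0.00 |

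These rows restate the identity; they are not evidence about this cohort. For scale, one point is the article's own threshold for deterioration.

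**Step 5. Can the fix be carried out?** NIHSS and KPS are both on the baseline, 6-week, 3-month and 6-month forms, so changes in both can be computed at each follow-up visit.

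**The case against.** The strongest reply is that Secondary study parameters is shorthand. It says that the oncofunctional outcome will be evaluated, that outcome has already been defined, and the x-axis wording is loosened in the same sentence without changing the variable. The text never says that uncorrected visit scores will be plotted. This has some force: the visit-score reading is likely, given how the article uses the term elsewhere, but it is not explicit. The shorthand argument does not explain KPS.

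A second reply is that little depends on the plot. It is descriptive and belongs to a secondary outcome. The main functional comparison, NIHSS deterioration, is already measured against baseline and analysed by logistic regression. This stands and limits the weight of the point.

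A third reply is that the change score is no cure. NIHSS has a floor of 0, so a patient who starts at 0 cannot improve while one with a deficit can. Delta NIHSS can therefore also depend on baseline. This stands too: the zero gaps in delta above follow from assuming equal change in both arms.

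Three stronger readings are tempting and are not supported:

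- **That the plot will present baseline differences as surgical results.** This needs both that visit scores are plotted and that the arms differ at baseline. The first is not explicit, and the documents give no figures on the second. Even then, a postoperative score still reflects surgery as well as the starting point.
- **That the choice between NIHSS and KPS is being held until the data are seen.** Nothing says so; the wording also allows both plots to be shown.
- **That the surgeon simply picks the technique.** The forms record the surgeon's reason for the modality, but the article also states a 1:1:1 ratio and assigns the task of group allocation to study staff. The point needs only the statement that allocation is not randomised.

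**Conclusion.** The contradiction is real, and it is minor. The defined y-axis is delta NIHSS. The planned y-axis is neurological status or KPS, and KPS does not occur in the definition. This is a conflict between two statements in the article, not detail left to a fuller document.

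If the analysis text is followed literally, any baseline difference between the non-randomised arms could enter the plot one for one: d points in mean visit NIHSS against 0 in mean delta NIHSS, assuming equal surgical effect. The value of d is unknown. The 0 to 2 points used above are an assumption for illustration. No test, error rate or sample size is affected. The conclusion about definition and analysis rests on the text alone; the conclusion about baseline carry-over also rests on reading status as the score at a visit.

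**What to change.** In Secondary study parameters, put delta NIHSS, stated as change from baseline, on the y-axis, as Secondary outcome measures defines it. If KPS is to be kept, show change in KPS from baseline as a separate supportive plot, labelled as additional to the defined outcome.

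The cost is a change of wording. No new data are needed, since both scales are already recorded at baseline and at the three follow-up visits. The change removes an additive baseline gap. It does not remove all confounding, so the plot should still be read as a descriptive comparison of non-randomised arms.
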